#### Randomisation/blinding

Participants will be blinded to condition. They will be generally informed that they will be randomised to ‘either one of two types of self-help interventions based on CBT’, not knowing any difference between the conditions. After baseline measurements, included participants will be allocated randomly (1:1) to therapist-guided or self-guided treatment in consecutive even-numbered blocks. Randomisation will be based on a true random number service and conducted by a person blinded to the participants, who is not otherwise involved with the study, using a true random number generator (http://www.random.org). It is impossible for the psychologist performing the inclusion assessment to anticipate participant allocation.

#### Measurements

The outcome measures are based on those used previously by Hedman-Lagerlöf *et al*
17 and Kern *et al*,^19^ for the evaluation of CBT interventions for AD. The battery of instruments in the current study overlaps with the recently published harmonising measures for eczema criteria, but have several additional measures, and does not include some of the suggested measures.^24^ We do include the suggested measurements for self-reported symptoms and quality of life but have no clinician-rated measurement of symptoms, which we acknowledge as a weakness.

##### Primary outcome measure

POEM^20^ measures the severity of symptoms of AD, which has a range of 0–28. The POEM has excellent psychometric properties and is widely used.^25^ In this study, in order to be conservative, response is operationalised as a POEM score reduction 4 points or more, and the non-inferiority margin is operationalised as 3 points. This is the same as earlier studies of CBT for AD, based on changes from severe eczema. Another evaluation has found smaller changes, around 2.1–2.9 as ‘likely to be beyond measurement error but unlikely to be clinically important’.^26^ Because of this, as we are including participants with mild, moderate and severe eczema, we could possibly have chosen an even smaller margin.

##### Secondary outcome measures

Demographical data will be collected on screening. Peak pruritus Numerical Rating Scale^27^ is used to measure itching sensations; Perceived Stress Scale^28^ is used to measure general experience of stress; Patient Health Questionnaire-9^29^ is used to measure depressive symptoms; Dermatological Life Quality Index^30^ is used to measure AD-specific quality of life; Insomnia Severity Index^31^ is used to measure severity of sleep problems and possible insomnia; Client Satisfaction Questionnaire-8^32^ is used to measure how satisfied participants are with the intervention. We will also ask participants to report if they experience adverse events associated with the treatment (AE). In addition to this, we will use the Credibility/Expectancy Scale^33^ to measure credibility. At the end of the intervention, the participants will be asked to estimate the Time spent in the Exercises (ToE). Euro-QOL Five Dimensions (EQ-5D)^34^ will be used to assess quality of life from a health economics perspective. Treatment Inventory of Costs in Psychiatric Patients (TIC-P)^35^ will be used to assess healthcare costs. Participant will also rate their user experience of the interventions with the System Usability Scale.^36^ Resource use is measured by the time in minutes the clinician spends on the different tasks associated with administering the intervention, doing interviews, and giving support, or Time spent on Treating. Therapists will register their time spent throughout the intervention, and not at a specific measurement point.

Outcomes at all scales will be compared with available published results regarding other internet-based interventions for each scale.

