#### Measurement points

Please refer to table 1. There are no planned interim analyses. There are no predefined criteria for trial termination.

**Table 1 T1:** Measurement points

Screening	Pre	Weekly	Week2	MID	POST	FU6	FU12
Demo	POEM	POEM	CES	POEM	POEM	POEM	POEM
POEM	NRS	NRS		NRS	NRS	NRS	NRS
NRS	DLQI	DLQI		DLQI	DLQI	DLQI	DLQI
DLQI	PHQ-9	PHQ-9		PHQ-9	PHQ-9	PHQ-9	PHQ-9
PHQ-9	PSS	PSS		PSS	PSS	PSS	PSS
	ISI	ISI		TIC-P	TIC-P	TIC-P	TIC-P
	TIC-P			EQ-5D	EQ-5D	EQ-5D	EQ-5D
	EQ-5D			ISI	ISI	ISI	ISI
					CSQ-8		
					AE		
					ToE SUS		

AE, adverse events; CES, Credibility/Expectancy Scale; CSQ-8, Client Satisfaction Questionnaire-8; Demo, demographical data; DLQI, Dermatological Life Quality Index; EQ-5D, Euro QOL 5 Dimensions; ISI, Insomnia Severity Index; NRS, Numerical Rating Scale; PHQ-9, Patient Health Questionnaire 9 item; POEM, patient-oriented eczema measure; PSS, Perceived Stress Scale; SUS, System Usability Scale; TIC-P, Treatment Inventory of Costs in Psychiatric Patients; ToE, Time (spent) on Exercises.

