#### Safety considerations

Participants’ regular healthcare is unaffected by either of the study conditions. Possible benefits for patients with increased ability to manage their disease are presumed to justify any disadvantages in the form of time consumption and temporary discomfort. Adverse treatment effects will be examined after the total twelve weeks of the intervention, and will be acted on if they are spontaneously reported before. If the disease worsens, the participants will be encouraged to seek help from their regular specialist clinic or primary healthcare centre. All communication and data storage take place on an encrypted and secure digital platform and is in accordance with the Karolinska Institutet’s regulations and the EU General Data Protection Regulation. In case of any serious harm, the standard patient’s insurance for Government financed healthcare will be applicable to every participant.

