## Ethics and dissemination

The study will be carried out according to the predefined standards of this trial protocol, the Declaration of Helsinki and Good Clinical Practice. This study will be reported according to the CONSORT statement for non-pharmacological trials.^41^ The interventions that will be administered have deemed safe by consultant dermatologists and have been previously evaluated without serious AEs.^18 19^ This study will use the Vancouver criteria for authorship. The results of this study will be published in peer-reviewed scientific journals, be presented to the scientific community at conferences. The results will also be communicated to study participants, patient organisations and clinicians.

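### The only scheduled adverse-event measure counts just the events that participants link to the treatment, so events put down to other causes are not counted as adverse events

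*Protocol article*

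**What the plan says.** In the protocol article, Secondary outcome measures gives the adverse-event outcome in one sentence: "We will also ask participants to report if they experience adverse events associated with the treatment (AE"). Safety considerations uses the same scope: "Adverse treatment effects will be examined after the total twelve weeks of the intervention, and will be acted on if they are spontaneously reported before". Table 1 (Measurement points) lists AE in the post-treatment column only. It does not appear in the weekly, mid-treatment, 6-month or 12-month columns. The table legend is broader and reads only "AE, adverse events", so the article states two scopes for one measure.

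On worsening disease, Safety considerations says that participants will be encouraged to seek help from their usual care. It does not say that worsening is entered as an adverse event. Nothing in the article describes collecting events regardless of cause, or judging relatedness as a separate step.

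Other measures carry no question about cause. POEM "measures the severity of symptoms of AD, which has a range of 0–28", PHQ-9 "is used to measure depressive symptoms" and ISI "is used to measure severity of sleep problems and possible insomnia". Table 1 schedules these three, together with itch NRS, DLQI and PSS, weekly and at mid-treatment, post-treatment and both follow-ups, without distinguishing the arms. TIC-P (healthcare costs) is collected before treatment and at mid-treatment, post-treatment and both follow-ups.

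**The concern.** Randomisation separates treatment effects from background events without anyone having to judge the cause of a single event. That works only if events are collected whatever their presumed cause. Filtering on attribution first turns a comparison of event rates into a comparison of rates multiplied by the probability of attribution.

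Individual attribution is hard in this trial. The Background section says that people with AD have a raised risk of depression and anxiety and that scratching follows mood, so background events and reactions to exposure exercises can look alike. The trial also asks whether therapist guidance can be removed, and self-care participants choose or create their own exposure exercises. Readers of a non-inferiority result will want to know whether removing guidance brings more harm. An adverse-event table limited to attributed events answers that weakly.

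**Working it through.** The article gives no adverse-event rate, so there is no figure to reproduce. The check is a comparison of passages, followed by an illustration on assumed values.

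**What each kind of event leaves in the data**

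| Event put down to another cause | Counted as an adverse event? | Recorded elsewhere (Table 1)? |
|---|---|---|
| Eczema flare | No | Yes: POEM and itch NRS, weekly and at later visits |
| Low mood | No | Yes: PHQ-9, weekly and at later visits |
| Poor sleep, stress | No | Yes: ISI and PSS, weekly and at later visits |
| Skin infection, injury | No | No dedicated scale; indirectly through TIC-P if care was used |
| Anxiety during exposure | No | No measure described as an anxiety scale |

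The loss has two parts. Worsening eczema and mood lose their status as adverse events but stay in the data as scores. Events with no scale may leave little or no trace. The analysis sections (Non-inferiority, Resource utilisation, Cost-effectiveness, Mediation) model change, costs and process. None describes a count of participants who deteriorate, and mean change can hide individual worsening.

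**Could the filter differ by arm?** Differences between study conditions gives guided care continuous text contact with a therapist plus two telephone evaluations. Self-care has clinician contact before the intervention and at 8 weeks. Digital self-care adds that the coordinator monitors the process and may contact inactive participants. The contact is unequal, but the post-treatment item is scheduled identically for both arms.

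**Illustration.** All rates here are assumptions. Let p be the true proportion of participants with an event and a the probability that it is attributed to treatment. Then

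recorded proportion = p × a.

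With equal p in both arms, the spurious difference is p × (a_guided − a_self):

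| p | 50/50 | 60/40 | 70/30 |
|---|---|---|---|
| 20% | 10% v 10%: 0 | 12% v 8%: 4 points | 14% v 6%: 8 points |
| 30% | 15% v 15%: 0 | 18% v 12%: 6 points | 21% v 9%: 12 points |
| 40% | 20% v 20%: 0 | 24% v 16%: 8 points | 28% v 12%: 16 points |

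(Columns are attribution in guided/self-care; cells are recorded guided v self-care.) With 174/2 = 87 per arm, p = 30% and a 60/40 split, the counts are 87 × 0.18 = 15.7 and 87 × 0.12 = 10.4. If the attribution pattern is reversed, the sign reverses.

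Now let true rates differ, 30% in self-care and 20% in guided care:

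- attribution 50% in both arms: 15% v 10%, so a 10-point excess appears as 5 points;
- 30% in self-care and 50% in guided care: 0.30 × 0.30 = 9% v 0.20 × 0.50 = 10%, so the excess disappears;
- 50% in self-care and 30% in guided care: 0.30 × 0.50 = 15% v 0.20 × 0.30 = 6%, so it appears as 9 points.

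Even with equal attribution, half of the events go uncounted at a = 50%, and a real difference is halved.

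**The case against.** The strongest objection is Table 1. A reader might infer that flares and low mood go unrecorded unless blamed on treatment. That is wrong: POEM, itch NRS and PHQ-9 are collected weekly in both arms with no question about cause, and deterioration by arm can be tabulated from planned data. It follows that the randomised comparison of eczema and mood is not lost either. This objection stands, and it confines the point to what is counted as an adverse event and to events that no scale covers.

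A reader might also infer that attribution does differ by arm. The documents do not show it. Randomisation/blinding says participants do not know how the conditions differ, and self-care participants do have a coordinator and a week-8 clinician contact. Unequal contact bears most directly on spontaneous reports; its effect on answers to the post-treatment item is conjecture.

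The commitment "The study will be carried out according to the predefined standards of this trial protocol, the Declaration of Helsinki and Good Clinical Practice" might be read as breached. The article gives no adverse-event definition under that heading, so a breach would rest on an outside source and is not claimed.

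The form itself is not shown, and a full protocol may hold broader wording. That stands as a caveat. Still, the article states the scope in two places, and both are narrow. Finally, the trial has no safety hypothesis and the interventions were previously evaluated without serious adverse events. This lowers the priority of the point but does not remove it.

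**Conclusion.** The point holds in a limited form. As described, the one scheduled adverse-event measure counts only events that the participant links to the treatment. Other events are not counted as adverse events. Eczema and mood worsening survive as scores without a described by-arm analysis of deterioration, and events without a scale may be missed. Differential attribution by arm is possible but not shown.

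The size is unknown. The 0 to 16 point range depends wholly on assumed event rates of 20% to 40% and attribution splits from 50/50 to 70/30. It describes the adverse-event count, not the POEM or PHQ-9 data. The conclusion also assumes that the article's wording reflects the form in use. The primary non-inferiority analysis is unaffected. What is weakened is any statement about comparative safety made beside it, so the change is worth making.

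**What to change.** 1. At post-treatment, ask about any new or worsened physical or psychological health problem since the start of the intervention, whatever its cause. Ask about severity, whether care was sought, and perceived relation to the intervention as separate follow-up items. If the form already does this, correct the article's description and align it with the Table 1 legend.
2. Make all-cause events by arm the main safety table, with treatment-attributed events as a secondary listing.
3. Tabulate individual worsening on POEM and PHQ-9 by arm, with cut-offs fixed before outcomes are seen by arm. For POEM, the article's 4-point response threshold could be mirrored as a rise of 4 or more. The article gives no PHQ-9 threshold, so one must be specified.

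The cost is one reworded online item with short follow-ups and two tables. More unrelated events will be reported, and completion will take slightly longer. The first cohort started on 5 December 2022, and 12 weeks (84 days) later is 27 February 2023, so some participants may already have answered the existing wording. Their adverse-event data must be reported separately and not pooled with the new item. The POEM and PHQ-9 table needs no new data and is unaffected by the change.

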#### Measurement points

Please refer to table 1. There are no planned interim analyses. There are no predefined criteria for trial termination.

**Table 1 T1:** Measurement points

Screening	Pre	Weekly	Week2	MID	POST	FU6	FU12
Demo	POEM	POEM	CES	POEM	POEM	POEM	POEM
POEM	NRS	NRS		NRS	NRS	NRS	NRS
NRS	DLQI	DLQI		DLQI	DLQI	DLQI	DLQI
DLQI	PHQ-9	PHQ-9		PHQ-9	PHQ-9	PHQ-9	PHQ-9
PHQ-9	PSS	PSS		PSS	PSS	PSS	PSS
	ISI	ISI		TIC-P	TIC-P	TIC-P	TIC-P
	TIC-P			EQ-5D	EQ-5D	EQ-5D	EQ-5D
	EQ-5D			ISI	ISI	ISI	ISI
					CSQ-8		
					AE		
					ToE SUS		

AE, adverse events; CES, Credibility/Expectancy Scale; CSQ-8, Client Satisfaction Questionnaire-8; Demo, demographical data; DLQI, Dermatological Life Quality Index; EQ-5D, Euro QOL 5 Dimensions; ISI, Insomnia Severity Index; NRS, Numerical Rating Scale; PHQ-9, Patient Health Questionnaire 9 item; POEM, patient-oriented eczema measure; PSS, Perceived Stress Scale; SUS, System Usability Scale; TIC-P, Treatment Inventory of Costs in Psychiatric Patients; ToE, Time (spent) on Exercises.

#### Safety considerations

Participants’ regular healthcare is unaffected by either of the study conditions. Possible benefits for patients with increased ability to manage their disease are presumed to justify any disadvantages in the form of time consumption and temporary discomfort. Adverse treatment effects will be examined after the total twelve weeks of the intervention, and will be acted on if they are spontaneously reported before. If the disease worsens, the participants will be encouraged to seek help from their regular specialist clinic or primary healthcare centre. All communication and data storage take place on an encrypted and secure digital platform and is in accordance with the Karolinska Institutet’s regulations and the EU General Data Protection Regulation. In case of any serious harm, the standard patient’s insurance for Government financed healthcare will be applicable to every participant.

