#### Guided care

The aim of CBT for AD is to target behavioural and emotional processes, to improve AD symptoms and increase quality of life. The participants read education material, and use worksheets and homework reports. The material is in Swedish and is currently only available to study personnel and participants. This intervention consists of 10 modules and lasts 12 weeks. An introduction provides information about CBT and AD. Participant register itching and scratching behaviours, with the aim to increase awareness of these behaviours. Gradually, the participants are introduced to the proposed active treatment components: mindfulness training and exposure with response prevention. Mindfulness is trained throughout the intervention. The purpose of mindfulness is to increase awareness of emotional and behavioural reaction patterns, and to increase tolerance of aversive inner experiences.^21^ Additionally, mindfulness training may improve stress tolerance. Participants are also trained in self-compassion, to increase understanding of one’s own reactions and to increase the ability to handle difficult situations in the treatment and life.^22^ After practising these fundamental skills, exposure with response prevention is introduced in week 4. Exposure is a controlled way to gradually approach situations that evoke strong emotions or somatic reactions. The purpose is to gain knowledge and experience in how this approach can change one’s perception of unwanted situations, emotions or somatic reactions.^23^ The assumption is that skills learnt from mindfulness practice and self-compassion training helps the patient to conduct exposure exercises. Response prevention means to reduce scratching in these problematic situations in order to reduce itch in the long term. Through this whole process, the participant is guided by a therapist. The therapist may be contacted through a secure internet platform at any time and responds within 48 hours. Participants read the education material, construct exercises to perform, describe their progress in homework assignments and receive feedback from their therapist. During the 12-week period, the participants work at their own pace, and contacts their therapist when necessary. The recommended pace, however, is one module per week, and the therapist contact participants who are inactive. All participants have access to the same treatment material but will construct exposure exercises that fit their specific situation, assisted by the therapist. The therapists will guide participants to make exercises as faithful to the treatment as possible. Participants will report back what they have done. Because therapist and participants never meet, there is no control of whether participants actually perform exercises as they are reported. The study coordinator will offer guidance to other therapists if needed.

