
#### Digital self-care

As with guided care, the aim of CBT for AD is to target behavioural and emotional processes, to improve AD symptoms and increase quality of life. The material is similar to guided care but shortened. Likewise, participants, read information and perform exercises in their everyday life. As with guided care, the main treatment components are mindfulness and exposure with response prevention, with a specific focus on itch. Participants will be able to practice mindfulness with the help of instructions and examples. Because it may be challenging to construct relevant exposure exercises without the help of a therapist, participants will receive detailed instructions and guidance, and get to choose exposure exercises from a long list of examples. They will also be free to create their own relevant exposure situations within the intervention. Digital self-care consists of eight modules. The only active interventions, mindfulness and exposure are introduced weeks 1 and 2, respectively. From weeks 3 to 7, no new interventions are introduced and participants are advised to continue practising the interventions, but there is a new theme of education each week, to act as inspiration for exercises. The last 4 weeks, the participant is merely advised to continue practice. There is no therapist, but the study coordinator monitors the process and may contact inactive participants. Participants will access the same digital platform as the guided condition. Participants work entirely at their own pace. Modules will be unlocked automatically if 1 week has passed, and all material in the previous module has been read. Participants will report if they have done their assignments, but there is no control if they do as they report.

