#### Differences between study conditions

The main differences between the conditions are that digital self-care (A) has contact with a clinician at only two points in time: preintervention and after 8 weeks plus the addition of automated messages, whereas guided care has continuous contact throughout the treatment via text messages on a secure platform and that (B) the treatment text is significantly shortened. Automated emails are sent every week to the non-guided group, consisting of a greeting and some encouraging words relevant to the week’s content. Both groups receive automated text messages at the time of new assessments. Guided care will also have an evaluation from a clinician via telephone at two points in time. Furthermore, digital self-care uses a mobile optimised interface, and have improvements in design aimed to decrease the need of guidance.

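### Adverse events are asked about only once, at POST, so POST non-responders may be under-counted and early effects are asked about late

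*Protocol article*

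**What the plan says.** Under Secondary outcome measures, the protocol article makes AEs a self-report item on treatment-related events. Table 1 (Measurement points) places that item in the POST column only; it is absent from Weekly, Week 2, MID, FU6 and FU12. Safety considerations agrees: "Adverse treatment effects will be examined after the total twelve weeks of the intervention", and effects before then "will be acted on if they are spontaneously reported before". The article does not say whether such early reports are recorded or counted.

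Contact during treatment differs by arm. In guided care, "The therapist may be contacted through a secure internet platform at any time and responds within 48 hours", and the therapist follows up inactive participants. In digital self-care, "There is no therapist, but the study coordinator monitors the process and may contact inactive participants". Under Differences between study conditions, self-care "has contact with a clinician at only two points in time: preintervention and after 8 weeks", whereas "guided care has continuous contact throughout the treatment via text messages on a secure platform". Guided care also has two clinician evaluations by telephone.

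Table 1 also schedules POEM, itch NRS, DLQI, PHQ-9, PSS and ISI weekly, without distinction between arms.

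**The concern.** Two features of the schedule limit what the trial can learn about harms.

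First, there is one solicited AE assessment, at the end of treatment. A participant who does not answer it leaves no solicited AE data. One who does answer must recall events from as early as the second week.

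Second, the only earlier route is unsolicited, and it runs through the contact that the trial varies by design. A participant already writing to a therapist has an easy occasion to mention a problem. A self-care participant has one clinician contact during treatment, after 8 weeks, and a coordinator whose follow-up of inactivity is optional.

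Removing the therapist is the contrast under test, and a non-inferior result would support care without one. Readers will therefore look at the harms table for any sign that self-care participants fared worse unnoticed. That table should not depend on how easy it was to report.

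**Working it through.** The article states no AE rate, AE count or AE power, so there is no plan figure to reproduce. What follows shows only how the mechanism works and what scale it could have.

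**Inputs from the article.** N = 174, allocated 1:1, so 174 / 2 = 87 per arm. The power calculation allows for 10% missing post-treatment data on the primary outcome. Exposure is introduced in week 2 (self-care) and week 4 (guided care). POST is at week 12.

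**Assumed.** The 10% applies equally to the AE item, since both belong to POST. AE risks, arm-specific missingness and capture by spontaneous report are illustrative.

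**Step 1: delay.** From the start of exposure to the first AE question: 12 − 2 = 10 weeks in self-care and 12 − 4 = 8 weeks in guided care.

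**Step 2: not asked.** 87 × 0.10 = 8.7 per arm; 174 × 0.10 = 17.4 in total.

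**Step 3: share of AE cases outside the solicited data.** With non-response m and a risk ratio R for non-responders against responders, the share is mR / [(1 − m) + mR].

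| m | R = 1 | R = 2 | R = 3 |
|---|---|---|---|
| 10% | 10% | 0.2/1.1 = 18% | 0.3/1.2 = 25% |
| 20% (assumed) | 20% | 0.4/1.2 = 33% | 0.6/1.4 = 43% |

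**Step 4: comparison of arms.** Assume AE risk 20% in POST responders and 40% in non-responders in both arms. Let s be the fraction of non-responders' events recovered by spontaneous report and counted. Per randomised participant, observed = 0.20(1 − m) + 0.40·m·s and true = 0.20(1 − m) + 0.40·m. Distortion is the observed difference (guided minus self-care) less the true difference, in percentage points.

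| m, guided / self-care | s, guided / self-care | Observed | True | Distortion |
|---|---|---|---|---|
| 10% / 10% | 0 / 0 | 18% / 18% | 22% / 22% | 0 |
| 10% / 10% | 50% / 0 | 20% / 18% | 22% / 22% | 2 |
| 10% / 10% | 100% / 0 | 22% / 18% | 22% / 22% | 4 |
| 5% / 15% | 0 / 0 | 19% / 17% | 21% / 23% | 4 |
| 5% / 15% | 100% / 0 | 21% / 17% | 21% / 23% | 6 |

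Fourth row in full: guided 0.20 × 0.95 = 0.19 observed, plus 0.40 × 0.05 = 0.02, gives 0.21 true; self-care 0.20 × 0.85 = 0.17 observed, plus 0.40 × 0.15 = 0.06, gives 0.23 true. With responders as the denominator, both arms show 20% (0.19/0.95 and 0.17/0.85), so the true 2-point difference disappears rather than reverses.

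The first row is the important one. With only the POST item counted and equal non-response, both arms are under-counted alike and the comparison is not distorted.

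**Step 5: set against chance.** At 20% in each arm, the standard error of a difference is √(2 × 0.20 × 0.80 / 87) = 6.1 points. The distortions above, 0 to 6 points, are at most about one standard error.

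**The case against.** The strongest reply is that the solicited item is the same question at the same time in both arms, and nothing in the article pools spontaneous reports with it. Safety considerations says that early reports lead to action; it does not say that they enter a between-arm count. This stands, and the first row of the Step 4 table supports it. A reader might infer from the unequal contact that AE data from the two arms cannot be compared. The article does not support that: it takes pooling, or unequal non-response at POST, to produce a bias.

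A reader might also infer that harms in dropouts go unrecorded. That is too strong as well. Stopping the modules is not the same as leaving POST unanswered. The article nowhere exempts people who stop from POST, the primary analyses are by intention to treat, and both groups get automated text messages when assessments are due. Only those who neither answer POST nor report spontaneously are lost to AE counting. Even for them, the weekly scales answered before they stopped remain, so worsening of symptoms or mood is partly observed on the same schedule in both arms.

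It is also fair to say that the interventions were previously evaluated without serious AEs (Ethics and dissemination), that a condensed article may leave AE handling to a fuller document, and that one assessment is a design choice rather than a mistake. These points lower the priority. They do not remove the gap: the article prints the schedule, with one solicited assessment, and assigns the weekly scales no safety use.

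**Conclusion.** The point holds in a limited form. AEs are solicited once. Participants who do not answer POST may be under-counted, and early effects are first asked about 8 to 10 weeks after exposure begins. Until then only spontaneous reports exist, and the route for them is stronger in guided care. A between-arm comparison is at risk only if those reports are counted or if non-response at POST differs by arm, in amount or in who is missing. In the scenarios shown, the error then makes self-care look safer relative to guided care than it is.

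The size is unknown, because the article gives no AE rates and no missingness by arm. Every percentage in Steps 3 and 4 rests on assumed values, apart from the 10% allowance, which was set for the primary outcome. This is a low-priority improvement and does not touch the primary analysis.

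**What to change.** 1. Add the AE item, worded as at POST, to the existing MID questionnaire in both arms. This shortens recall and gives solicited data on people who leave between MID and POST. It does not reach those who stop answering before MID.
2. State that the between-arm comparison of harms uses solicited items only, with the number answering in each arm as the denominator. List spontaneous reports separately by source (therapist, coordinator, clinician interview).
3. From the weekly POEM already collected, tabulate by arm the share whose score rises by 4 points or more from baseline, mirroring the response definition under Primary outcome measure. State whether any week or the last available score is used. As POEM ends at 28, note how many start above 28 − 4 = 24 and so cannot meet the threshold.

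Cost: one item at an existing online assessment, one sentence and one table. There is slight extra response burden. Recruitment has begun, so the first change needs a minor amendment and gives MID data only for participants who reach MID after it. The second and third need no new data.
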